## Methods

### Trial Design

This study is an individually randomized, parallel, 2-group therapy trial. A total of 132 veterans will be randomized in a 1:1 fashion to either a Deprexis intervention or a TAU control group.

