### Sample Size

#### Aim 1

In determining the sample size for qualitative studies, the key goals are to develop case-oriented perspectives, select participants with a range of characteristics and perspectives, and achieve saturation (ie, the point at which subsequent interviews fail to produce new themes) [56]. Research indicates that typically, saturation is reached with 12 to 16 interviews. As we are also obtaining qualitative data on veterans who did not adhere to the treatment (approximately 23% of the sample), we increased our recruitment target slightly to 16 to 20 veterans to allow for a sufficient sample of veterans who completed Deprexis treatment, as well as those who terminated treatment early (ie, did not complete the posttreatment or follow-up questionnaires).

#### Aim 2

Effect sizes in the general population Deprexis RCT for participants with mild to moderate depression (QIDS-SR-16 score <21) ranged from Cohen *d*=0.65 to Cohen *d*=0.90. Some evidence suggests that effect sizes for psychological interventions may be smaller for veterans [57]; therefore, we estimate that effect sizes are at least medium (Cohen *d*=0.50) for measures of functioning and large (Cohen *d*=0.80) for depressive symptoms. To achieve 0.8 power at an α of .05, a total of 102 participants need to be recruited. Accounting for 23% attrition over time, we will randomize 132 participants at baseline. In the general population trial, approximately 57% (n=213) of the randomized participants were high engagers (>90 min), and effect sizes were slightly higher in the high engager group (Cohen *d*>0.67) than in the overall sample. Thus, we expect to be adequately powered for analysis in this subgroup.

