### Assignment of Intervention: Allocation and Blinding

#### Allocation Sequence Generation

Computer-generated stratified block randomization with block sizes of 4 and 8 will be performed by the research technician using a web-based application. As depression severity has previously been associated with Deprexis treatment response, randomization will be stratified by depression severity, consisting of 3 categories: mild=QIDS-SR-16 score 6-10, mild to moderate=QIDS-SR-16 score 11-15, and moderate=QIDS-SR-16 score <16-20. Stratification was limited to depression severity because minimizing the number of strata is recommended in trials that enroll relatively few participants.

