For aim 2, linear mixed effects regression [60] with restricted maximum likelihood estimation will be used to model continuous outcomes (eg, changes in psychosocial functioning outcomes and depressive symptoms), and logistic models will be used to model changes in dichotomous outcomes (eg, significant change: ≥50% improvement in scores) over time. Linear mixed effects regression models will initially be fit using an interactive model (eg, treatment condition+time+treatment condition×time) and compared to an additive model (eg, treatment condition+time) using a likelihood ratio test. This nested comparison serves as a significance test of the treatment×time interaction and will be reported as such in the analyses [61]. *Condition* (treatment or TAU), *time* (before treatment, after treatment, and follow-up), and their interaction will be entered as fixed effects, and *participant* will be entered as a random effect (ie, random intercepts). Cohen *d* for the treatment×time interaction will be calculated using an effect size derived from the mean pretreatment-to-posttreatment and follow-up change in the treatment condition minus the mean pretreatment-to-posttreatment and follow-up change in the TAU control divided by the pooled pretreatment SD [62]. Simulations suggested that this effect size estimate was the most stable and robust for these types of treatment designs [63]. When comparisons are made within a time period, Welch 1-tailed *t* tests will be performed because they are ideal when the 2 samples have unequal variances or unequal sample sizes [64]. When comparisons are made within a treatment condition over time (repeated measures), a paired samples *t* test will be performed. As participants can engage in nonstudy mental health treatment, nonstudy treatment use will be included as a covariate in all analyses.

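### The primary mixed model gives each arm its own baseline mean, so it tests a difference in change scores; adjusting for the baseline score already collected would be more precise at no cost

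*Protocol article*

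**What the plan says.** In the protocol article, Statistical Methods, the aim 2 model for continuous outcomes has condition, time and their product as fixed effects. The three time levels include the pretreatment visit: "before treatment, after treatment, and follow-up), and their interaction will be entered as fixed effects". The only random effect is a participant intercept. The treatment effect is tested by a likelihood ratio comparison with an additive model, which also keeps the condition main effect. The effect size uses the same contrast: mean change in one arm minus mean change in the other, "divided by the pooled pretreatment SD". Nonstudy treatment use is the only covariate named for all analyses.

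Under Allocation Sequence Generation, "randomization will be stratified by depression severity, consisting of 3 categories", because severity had been associated with response to Deprexis. The Statistical Methods text does not name that stratum as a model term.

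Under Sample Size, the assumed "effect sizes are at least medium (Cohen *d*=0.50) for measures of functioning and large (Cohen *d*=0.80) for depressive symptoms" lead to: "To achieve 0.8 power at an α of .05, a total of 102 participants need to be recruited". Then: "Accounting for 23% attrition over time, we will randomize 132 participants at baseline". Sidedness is not stated there. Its only mention is in Statistical Methods: "When comparisons are made within a time period, Welch 1-tailed *t* tests will be performed".

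**The concern.** With the pretreatment score as an outcome and a free condition effect, the interaction subtracts the observed baseline difference in full from the later difference. Under 1:1 randomization the expected baseline difference is zero, so full subtraction over-corrects whenever the baseline-to-follow-up correlation is below 1. An adjusted analysis subtracts only the predictable part. What is at stake is power on WHODAS-II and SDS, whose d=0.50 sets the sample size.

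Two smaller points belong to the same model. A random intercept alone forces equal variances and equal correlations across the three visits. And the factor used to stratify the randomization is absent from the stated model.

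**Working it through.** **Inputs from the article.** d=0.50 for functioning and 0.80 for depressive symptoms; α .05; power 0.8; 102 evaluable, so 51 per arm; 132 randomized; 23% attrition; 1:1 allocation. **Assumption.** The correlation r between baseline and a later visit is not given; I use r=0.3 to 0.7, with equal SDs set to 1.

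**1. The plan's own figure.** A two-sample t test at d=0.50 and 80% power needs 102 in total one-sided and 128 two-sided. With 51 per arm, power is 80.6% one-sided and 70.6% two-sided. So 102 reproduces only as one-sided. Attrition: 102/(1−0.23)=132.5, in line with the stated 132.

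**2. Variance of the treatment contrast, per participant.**
- Planned model, change score: 2(1−r).
- Common baseline mean, or baseline as covariate: 1−r².
- Ratio: (1−r²)/[2(1−r)] = (1+r)/2. This is below 1 for every r<1; for example, 0.75 at r=0.5.

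**3. Power for one post-baseline contrast.** Noncentral t, 51 per arm, two-sided .05. The standardized effect is 0.50 divided by the square root of the variance in step 2.

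| r | effect, planned | power, planned | effect, adjusted | power, adjusted |
|---|---|---|---|---|
| 0.3 | 0.50/1.183=0.423 | 56% | 0.50/0.954=0.524 | 75% |
| 0.4 | 0.50/1.095=0.456 | 63% | 0.50/0.917=0.546 | 78% |
| 0.5 | 0.50/1.000=0.500 | 71% | 0.50/0.866=0.577 | 82% |
| 0.6 | 0.50/0.894=0.559 | 80% | 0.50/0.800=0.625 | 88% |
| 0.7 | 0.50/0.775=0.645 | 90% | 0.50/0.714=0.700 | 94% |

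At d=0.80 the planned contrast already has 92% at r=0.3 and 99.9% at r=0.7.

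**4. The planned two-degree-of-freedom test.** With equal effects at both later visits and equal correlations, power goes from 66% to 88% at r=0.4 and from 75% to 90% at r=0.5.

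**5. The stratum.** In a simulation of 120 trials at r=0.5, the standard error of the interaction in the planned model was 0.1974 with and without a stratum main effect. Constraining the baseline lowered it to 0.171; adding the stratum as well lowered it to 0.166.

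**6. The random-intercept covariance.** I assumed correlations of 0.5 (pre–post), 0.4 (pre–follow-up) and 0.75 (post–follow-up), with no treatment effect. The two-degree-of-freedom test rejects about 6% of the time and the pre-to-follow-up contrast about 9%. Results are similar with equal SDs and with SDs of 3.5/4.8/5.0.

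**The case against.** The planned model is conventional, its estimate is unbiased under randomization, and its effect-size definition matches it. All of that stands: this is a loss of precision, not an invalid analysis.

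Several stronger readings are tempting, and the article does not support them.

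- *The free baseline is why the trial falls short of 80%, and the fix restores it.* At r=0.5 the change-score variance is 2(1−0.5)=1, the same as a simple post-treatment comparison. The gap between 80.6% and 70.6% at that r is therefore entirely one-sided versus two-sided. The article never says that 80% was meant two-sided. Nor does the planned model always fall short: it reaches about 80% at r of about 0.6. After the fix the range is 75% to 94%, so a figure near 80% holds only for r around 0.4 to 0.5.
- *Omitting the stratum costs precision.* With complete data the interaction is a within-person contrast, and a stratum main effect cancels from it. For QIDS-SR-16 the stratum is also only a banding of that score.
- *Type I error is 9%.* That applies to one pairwise contrast under assumed correlations. The planned interaction test is nearer 6%.

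It is also fair that step 3 does not power the planned two-degree-of-freedom test, and that 51 per arm leaves out partly observed participants who enter the intention-to-treat analysis through imputation. Step 4 shows that the gain is in the same direction on the planned test.

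**Conclusion.** The point holds as a matter of efficiency. The variance ratio (1+r)/2 is algebra under equal visit variances, and the adjusted model is the more precise one at every r<1. How much power this buys depends on an r that the article does not supply: 19 percentage points at r=0.3, 11 or 12 at r=0.5 and 4 at r=0.7, for a single contrast at d=0.50 and two-sided .05. Depressive symptoms at d=0.80 have little to gain. The covariance restriction is a minor secondary issue that rests on assumed correlations. The missing stratum is a mismatch between randomization and analysis, not a material loss of precision. The unstated sidedness of the 102 is a separate matter that needs its own answer.

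**What to change.** In Statistical Methods, replace the model by one of two forms:

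- a constrained longitudinal model with a common baseline mean, that is, time plus condition-by-visit terms at posttreatment and follow-up only, with no condition effect at baseline; the likelihood ratio comparison is then against time alone; or
- a model of the posttreatment and follow-up scores with the baseline score as covariate.

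In either form, use an unstructured covariance over the visits, add the three-level QIDS-SR-16 severity stratum as a fixed effect, and report the adjusted difference at each later visit. Cohen d can still be scaled by the pooled pretreatment SD. Separately, state under Sample Size whether the 102 is one-sided or two-sided.

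The cost is wording. The primary outcomes and the stratum are already collected. The article reports 4 participants recruited and analysis expected in June 2029, so the change can be prespecified well before any outcome analysis.

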### Aims

Deprexis has not yet been rigorously evaluated with a veteran population in a VA medical center setting. This study aims to fill this critical gap in the literature by testing whether Deprexis is acceptable and effectively decreases depressive symptoms and improves functional outcomes in veterans (N=152) presenting for VA health care with mild to moderate depressive symptoms. The objective of aim 1 is to assess perceptions, needs, and preferences as they relate to Deprexis through conducting posttreatment assessment interviews with veterans (n=16-20) and identify the components that improve veterans’ experience and uptake of Deprexis. The results obtained in aim 1 will be used to inform the rollout of RCT procedures under aim 2. Aim 2a involves completing an RCT comparing an 8-week course of Deprexis to a treatment-as-usual (TAU) control condition. We hypothesize that veterans engaged in Deprexis will show improvements on measures of functioning and decreases in depressive symptoms compared to the TAU control group. To generate hypotheses for future study, the objective of exploratory aim 2b will be to examine whether demographic variables, baseline psychopathology, credibility, and Deprexis use moderate treatment effects on the primary outcomes.

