### Relevant Concomitant Care and Interventions That Are Permitted or Prohibited During the Trial

To participate, veterans need to be stable (no changes in the last 30 days) on medications prescribed for a mental health disorder. Veterans randomized to either treatment group are allowed to start or continue any nonstudy treatment resources, including mental health treatment, during their participation in the trial.

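### The follow-up t tests cannot carry the covariate required in all analyses, and the within-arm paired tests have no stated role and cannot isolate a Deprexis effect

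*Protocol article*

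**What the plan says.** All the relevant analysis text is in one paragraph of the protocol article, under Statistical Methods.

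- **Formal test.** For continuous outcomes, a random-intercept linear mixed model with condition, time and their interaction is compared with the additive model by a likelihood ratio test: "This nested comparison serves as a significance test of the treatment×time interaction and will be reported as such in the analyses".
- **Comparison of arms at one visit.** "When comparisons are made within a time period, Welch 1-tailed *t* tests will be performed". The reason given is robustness to unequal variances or group sizes.
- **Change within one arm.** "When comparisons are made within a treatment condition over time (repeated measures), a paired samples *t* test will be performed".
- **Covariate rule, in the next sentence.** "nonstudy treatment use will be included as a covariate in all analyses". No exception and no adjusted version of either t test is given.

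Two other sections bear on this. Aims states the hypothesis against the control arm: Deprexis participants "will show improvements on measures of functioning and decreases in depressive symptoms compared to the TAU control group". The section on concomitant care says that veterans in both arms "are allowed to start or continue any nonstudy treatment resources, including mental health treatment, during their participation in the trial".

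**The concern.** There are two linked problems.

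First, consecutive sentences conflict. Paired and Welch t tests are unadjusted by construction, yet the covariate is required everywhere. An analyst must either break the covariate rule or replace the t tests with another procedure. If the t tests are run as written, an arm difference from the adjusted model and one from an unadjusted Welch test can disagree, and the text does not say which prevails.

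Second, the paired tests do not address the stated hypothesis, because a test within one arm has no comparator. Many participants are approached after a positive PHQ-2 screen, all enter on a QIDS-SR score of 6 to 20, and both arms may use other care. Some improvement without any Deprexis effect is therefore plausible, at least for depressive symptoms. A small p value within the Deprexis arm, set beside a nonsignificant one in TAU, is easily read as efficacy.

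**Working it through.** **Step 1. The two rules side by side.** A paired t test uses only the mean and SD of the within-person differences. A Welch t test uses only two means, two SDs and two sample sizes. Neither has a place for nonstudy treatment use. The covariate sentence covers all analyses without exception. The conflict follows from the wording and needs no calculation.

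**Step 2. Sample size for the illustration.** The Sample Size section gives 102 evaluable participants, and Trial Design gives 1:1 allocation, so 102 / 2 = 51 per arm. As a check on that figure, the section states "we estimate that effect sizes are at least medium (Cohen *d*=0.50) for measures of functioning and large (Cohen *d*=0.80) for depressive symptoms", with α .05 and power 0.8. For d = 0.50, a one-sided two-sample t test needs 50.15, rounded up to 51 per arm, or 102 in total, which matches. A two-sided test needs 63.77, rounded up to 64 per arm, or 128, which does not. Inflation for 23% attrition gives 102 / 0.77 = 132.5, against the stated 132. The sidedness behind 102 is a separate matter; only the 51 is used here.

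**Step 3. How often the paired test is significant with no treatment effect.** These inputs are assumptions, not document figures: the same natural improvement in both arms, expressed as dz (mean change divided by the SD of change), and a two-sided .05 paired test. The test statistic is noncentral t with 50 df and noncentrality dz × √51; the critical value is 2.009. The arms are independent, so if each is significant with probability p, the chance of significance in Deprexis but not in TAU is p(1 − p).

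| dz | noncentrality | p: significant in one arm | p(1 − p): Deprexis only |
|---|---|---|---|
| 0.2 | 1.43 | 28.8% | 20.5% |
| 0.3 | 2.14 | 55.6% | 24.7% |
| 0.4 | 2.86 | 80.0% | 16.0% |
| 0.5 | 3.57 | 93.8% | 5.8% |
| 0.6 | 4.29 | 98.8% | 1.2% |

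The last column cannot exceed 25% (reached at p = 0.5). It peaks near 0.3 SD and falls as improvement grows, because both arms then tend to be significant.

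**Step 4. Sensitivity to the scale.** If natural improvement is given in baseline SDs (g), and the SD is the same at both visits, dz = g / √(2(1 − r)), where r is the pre-post correlation. At r = 0.5, dz = g and the table applies unchanged. At r = 0.7, g of 0.2, 0.3 and 0.5 gives p of 44.0%, 77.4% and 99.5%, and Deprexis-only rates of 24.6%, 17.5% and 0.5%.

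**Step 5. Benchmark.** A between-arm test with no treatment effect favours Deprexis falsely in 2.5% of trials if two-sided at .05, and in 5% if one-tailed at .05, as the Welch tests would be if run at that level. These rates do not depend on natural improvement.

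**The case against.** The strongest reply is that efficacy is already judged between arms. The likelihood ratio test is of the interaction, the planned Cohen d is change in Deprexis minus change in TAU, and the hypothesis is stated against TAU. This stands. A reader might infer that the plan treats within-arm p values as evidence of efficacy, or uses significance in Deprexis only as a decision rule. The document says neither, so the rates above show what the paired tests cannot tell us; they are not the trial's false-positive rate.

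A reader might also infer that the t tests necessarily handle missing data differently from the model. For the intention-to-treat group this is not supported: the section on analysis populations plans multiple imputation there, and nothing excludes the t tests from the imputed data. The firm difference is in adjustment.

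A third inference would be that the Deprexis-only pattern is always far above the nominal rate. It is not: at 0.5 SD of change it is about 6%, and at 0.6 SD about 1%. Nor does the document establish that scores must fall in both arms. Flyers and providers also recruit, the WHODAS-II and SDS are not entry criteria, and the introduction cites high rates of progression to MDD.

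Finally, the covariate sentence could be read as meaning all regression models. That is a reasonable guess at the intention and would remove the conflict, but the text does not say it, and it would leave the paired tests without a role.

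**Conclusion.** The point holds, at low to moderate severity. The conflict between the t tests and the covariate rule is literal and rests on no assumption. The paired tests have no stated purpose and cannot separate a Deprexis effect from change that would occur anyway. With 51 per arm, no treatment effect and an assumed 0.2 to 0.5 SD of change, they are significant in 29% to 94% of trials, and significant in Deprexis only in about 6% to 25%. Those figures depend on the assumed natural improvement, which the document does not give. Severity is held down because the formal test is the between-arm interaction and the defect can be repaired in wording.

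**What to change.** Replace the two t-test sentences. Obtain the arm differences at each visit and the within-arm changes as contrasts (estimated marginal means) from the planned mixed model, on the same analysis set and the same imputed data. If unequal variances are a concern, let the residual variance differ by arm or visit. Report within-arm changes as descriptive estimates with 95% intervals, and state that conclusions on efficacy rest on between-arm contrasts.

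Replace the blanket covariate sentence with a list of the models that carry nonstudy treatment use. Do not force it into the main efficacy contrasts: such treatment may start during the trial, so the variable can arise after randomization, and adjusting for it can bias the treatment effect. A labelled supplementary model could carry it.

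The cost is wording and a little analysis work, with no change to sample size or data collection. Within-arm p values are lost. Welch's protection against unequal variances is also lost unless the model allows them.

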**Figure 1 figure1:**
[figure not shown]
Deprexis sample presentation.

Veterans randomized to the control condition will have access to standard VA treatment resources, including mental health treatment (they will be provided with a list of available resources).

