The PCL-5 [49] will be used to identify whether PTSD is a potential moderator of symptom change and to examine whether Deprexis produces meaningful changes in PTSD symptoms. The version of the PCL-5 used (PCL-5 with Criterion A) will include an assessment of the presence of a traumatic event meeting criterion A (the first criterion for diagnosing PTSD according to the Diagnostic and Statistical Manual of Mental Disorders, Fifth Edition). If no traumatic event is endorsed, veterans will not complete the remaining PCL-5 questions. Veterans who endorse exposure to a criterion A traumatic event will complete the 20-item PCL-5, which assesses PTSD symptom severity on a 5-point scale (eg, “In the past month, how much were you bothered by ‘Repeated, disturbing, and unwanted memories of the stressful experience?’”). Scores range from 0 to 80, with scores of >31 being indicative of probable PTSD (ref). The measure takes approximately 10 minutes to complete. The measure has excellent internal consistency (Cronbach α=0.94), high test-retest reliability (*r*=0.82) [49], and moderate convergent and discriminant validity (*r*=0.31-0.60) [49]. The PCL-5 is as sensitive to clinical change that occurs between pre- and posttreatment assessments as gold standard interview-based measures of PTSD symptoms (alerting convergent validity: *r*=0.94 and contrast converting validity: *r*=0.92) [50].

The following moderators and covariates are measured at baseline:

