#### Definition of Analysis Population Relating to Protocol Nonadherence and Any Statistical Methods to Handle Missing Data

Consistent with CONSORT (Consolidated Standards of Reporting Trials) recommendations [66], aim 2 analyses will be conducted across four groups: (1) the intention-to-treat group, which includes data from all randomized participants, regardless of treatment adherence or attrition; (2) the per-protocol group, which consists of participants who are considered treatment adherent, defined as ≥60 minutes of Deprexis use (which is consistent with previous research [29]); (3) the high-engagement group, which consists of participants who demonstrated strong treatment uptake, defined as ≥90 minutes of Deprexis use (this cutoff is approximately 1 SD below the mean for the treatment-adherent group in the general population Deprexis RCT); and (4) the completer group, which consists of participants who complete both baseline and posttreatment assessments. In the intent-to-treat group, the *Amelia II* (version 1.8.2) package in R [67] will be used to impute missing data with an expectation-maximization and bootstrapping algorithm. All available variables will be used to impute missing data, and the number of imputed datasets will be based on the proportion of missing data.

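### Nonstudy treatment use, on the natural reading measured after randomization and overlapping with the TAU comparator, is a covariate in all analyses; depending on its coding it adds nothing or can bias the intention-to-treat effect

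*Protocol article*

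**What the plan says.** The rule stands at the end of the aim 2 paragraph in Statistical Methods: "As participants can engage in nonstudy mental health treatment, nonstudy treatment use will be included as a covariate in all analyses". It does not say when use is measured, whether it is fixed or time-varying, or whether it interacts with time.

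Four other places bear on it:

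- Relevant Concomitant Care: veterans in either group "are allowed to start or continue any nonstudy treatment resources, including mental health treatment, during their participation in the trial".
- Intervention Description, control-condition paragraph: "Veterans randomized to the control condition will have access to standard VA treatment resources, including mental health treatment". Controls also receive a list of resources.
- Measures: the list introduced by "The following moderators and covariates are measured at baseline" does not include nonstudy treatment use.
- Definition of Analysis Population: the intention-to-treat group is the one "which includes data from all randomized participants, regardless of treatment adherence or attrition". The rule covers all analyses, so it covers this one.

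The treatment effect is tested by comparing the models with and without treatment×time: "This nested comparison serves as a significance test of the treatment×time interaction and will be reported as such in the analyses". No analysis without the covariate is named.

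**The concern.** The reason given for the adjustment is that participants are free to obtain other care while in the trial. That points to use after randomization. Such use can depend on the arm, because only controls are described as receiving a resource list and because a change in symptoms can change help-seeking. It can also depend on how a participant is doing, whatever the arm. Conditioning on it removes any part of the Deprexis effect that runs through other care, and it lets help-seeking by participants who are doing badly distort the comparison.

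The overlap with the comparator adds to this. Aim 2a compares Deprexis with usual care, and usual care includes the care being held constant. The adjusted contrast is therefore a different question. It is not a clean direct effect either, unless nothing unmeasured drives both care-seeking and outcome. The contrast that randomization protects would appear nowhere among the stated model-based analyses.

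**Working it through.** **The plan's own figure.** The Sample Size section assumes effects "at least medium (Cohen *d*=0.50) for measures of functioning" and states: "To achieve 0.8 power at an α of .05, a total of 102 participants need to be recruited". A two-sample t test with d = 0.50 and 51 per arm has power 0.806 at one-sided α .05 (0.706 two-sided), so 102 reproduces with a one-sided test. The point does not depend on this figure. It only supplies d = 0.50 as the reference effect.

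**Assumptions.** The article gives no uptake rates and no effect of other care. The values below are illustrative. The outcome SD is 1, negative values favour Deprexis, and the total effect is fixed at -0.50.

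**Formula.** For a linear analysis of change, with p_D and p_T the proportions using nonstudy care and β the within-arm coefficient of use:

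adjusted effect = total effect - β × (p_D - p_T)

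If other care lowers scores by g and use is otherwise unrelated to course, β = -g. If care is inert but worsening participants seek it, β is positive. The simulation below gives β = (-0.416 + 0.500)/0.20 = 0.42.

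**Results, 200,000 simulated participants per scenario.**

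| Use, Deprexis / TAU | Assumption | Formula | Simulated |
|---|---|---|---|
| 20% / 40% | g = 0.3 | -0.50 - 0.3×0.20 = -0.56 | -0.556 |
| 20% / 40% | g = 0.5 | -0.50 - 0.5×0.20 = -0.60 | -0.592 |
| 20% / 40% | g = 0.8 | -0.50 - 0.8×0.20 = -0.66 | -0.667 |
| 20% / 40% | inert care, worsening participants seek it | used to obtain β | -0.416 |
| 40% / 20% | g = 0.3 | -0.50 + 0.3×0.20 = -0.44 | -0.442 |
| 40% / 20% | g = 0.5 | -0.50 + 0.5×0.20 = -0.40 | -0.396 |
| 40% / 20% | g = 0.8 | -0.50 + 0.8×0.20 = -0.34 | -0.336 |
| 40% / 20% | inert care, worsening participants seek it | -0.50 - 0.42×0.20 = -0.58 | -0.582 |
| 30% / 30% | every combination tried | no shift | equal to unadjusted within 0.002 |

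The two mechanisms can offset each other: at 20% / 40% with g = 0.3 and symptom-driven seeking, the adjusted estimate is -0.474.

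**Three further cases with inert, symptom-driven care.**

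- Use 22% Deprexis, 41% TAU: -0.50 + 0.42×0.19 = -0.42.
- Same rates, true null: 0 + 0.42×0.19 = +0.08 SD, a spurious difference favouring TAU.
- Arm has no direct effect on seeking, and use differs (24% against 33%) only because Deprexis works: -0.50 + 0.42×0.09 = -0.46.

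**Coding in the mixed model.** A random-intercept model was fitted by REML to three visits, with use 20% / 40% and g = 0.5. The first post-baseline treatment×time estimates were:

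- no covariate: -0.495
- person-level main effect: -0.495
- time-varying covariate: -0.599
- covariate × time: -0.602

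With complete data, a person-level main effect acts only between participants, while treatment×time is estimated within participants. The estimate therefore cannot move.

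**Logistic responder model.** In an illustrative logistic model of response at a single endpoint, a person-level covariate moved the odds ratio from 2.33 to 2.05 (symptom-driven use), from 1.89 to 2.31 (helpful care) and from 1.01 to 0.87 (true null). Part of a shift away from the null can be non-collapsibility of the odds ratio. The shift under the null cannot.

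**Consequence for power.** By normal approximation at 51 per arm, the standard error is √(2/51) = 0.198. One-sided power at 0.50 SD follows from 0.50/0.198 - 1.645 = 0.88, which gives 0.81. At 0.416 SD it follows from 0.416/0.198 - 1.645 = 0.46, which gives 0.68.

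**The case against.** The strongest reply is that the simplest reading of Statistical Methods is a person-level main effect. On that reading the linear treatment×time test is unaffected, because the intention-to-treat data are imputed and therefore complete. This stands for that model. It does not rescue the rule: in this form the covariate contributes nothing to the test it was added for, and the protection does not carry over to the logistic models of 50% improvement.

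Second, the rule cannot apply literally everywhere. The article's Cohen d is a difference in mean changes over the pooled pretreatment SD, with no covariate term, and the Welch and paired t tests take none. This also stands. It means that the effect size and a covariate-adjusted test could describe different contrasts.

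Third, use during the trial is an inference. The article does not give the timing, and a purely baseline measure would remove the objection. The stated rationale, the concomitant-care section and the absence from the baseline list make the during-trial reading the natural one. If baseline use is meant, the sentence needs to say so.

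Fourth, a reader might infer that the plan certainly biases the result, or biases it in a known direction. The documents support neither. Both arms have the same permission to use other care. Background and Rationale itself suggests that a good experience with an internet intervention could ease a later move to traditional care, so use could be higher with Deprexis. If use is equal, the linear estimate does not shift.

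**Conclusion.** The point holds in conditional form. The article fixes a rule that adjusts every analysis for a variable that is, on the natural reading, post-randomization and part of the comparator, and it names no unadjusted primary analysis. The rule is redundant if the covariate is a time-constant main effect in the linear model with complete data. If it is time-varying, interacts with time or enters the logistic models, it can bias the intention-to-treat effect when use differs by arm, including when use differs only because it follows symptom course.

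Under assumed use of 20% against 40%, a true -0.50 SD is estimated at about -0.42 to -0.67. With the rates reversed the range is about -0.34 to -0.58. These ranges rest on assumed uptake and assumed effects of other care. They show what is possible and do not predict this trial's bias.

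**What to change.** Replace the sentence in Statistical Methods with three statements:

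1. The primary and confirmatory intention-to-treat models, linear and logistic, do not include nonstudy treatment use during the trial.
2. Mental health treatment status before randomization may be a covariate if it is collected. The Measures section describes no such item; the eligibility criteria cover only 30-day stability of psychotropic medication.
3. Nonstudy treatment use during the trial is reported by arm. A model adjusted for it is a labelled sensitivity analysis, with its timing and coding stated.

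During-trial use may stay among the variables that inform the imputation; the objection concerns the analysis model only.

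The cost is a change of wording, with no added participants and no change to the care that participants may receive. Only the optional baseline adjustment could need a new item, if treatment status is not already recorded. Four participants had been recruited at submission, so the change can be made well before the planned analysis.
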